# PROTOCOL SUMMARY

**Purpose:** The purpose of this study is to determine whether men in camps randomized to receive a microfinance and health leadership intervention have a lower incidence of sexually transmitted infections (NG, TV, CT) and report perpetrating less physical or sexual violence against female sexual partners as compared to men in camps not randomized to receive the intervention.

**Design:** Cluster-randomized trial.

**Study Population:** Young men ages 15 or older that are members of camps (social groups) in Dar es Salaam, Tanzania.

**Study Size:** 1249 male camp members

**Intervention:** 60 eligible camps will be randomized in to either a microfinance and health leadership intervention or a control condition. Eligible members in the intervention camps will be able to participate in intervention activities.

**Duration and Follow-up:** This a 5 year cluster-randomized study. Behavioral data will be collected at baseline, 12 months, and 30 months after intervention. Biological data will be collected at baseline and 30 months.

**Primary Objectives:** To determine whether men in camps randomized to receive a microfinance and health leadership intervention have a lower prevalence of sexually transmitted infections (NG, TV, CT) and report perpetrating less physical or sexual violence against female sexual partners as compared to men in camps not randomized to receive the intervention.

**Primary Endpoints:** Incidence of STIs (NG, TV, CT) and perpetration of sexual violence against female sexual partners.

**Secondary Endpoints:** HIV risk and protective behaviors including: gender equity, alcohol and drug use, sexual relations and risk behavior, uptake of HIV counseling and testing; unprotected sexual intercourse; consistent condom use; delay of sexual debut; number of sexual partners, and sexual concurrency.

**Mediators**: In the event that program effects are identified, the degree to which the following mediate the multi-level intervention on STI and gender-based violence: hope, future orientation, social cohesion, collective efficacy, social support, emotional distress, sexual networks, social support and social influence.

**Qualitative:** Qualitative interviews with study participants will add contextual data for understanding various aspects of participant beliefs, attitudes, and behaviors towards endpoints measured.

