### 3.2.3 Second Primary Aim

To achieve our second primary aim, to evaluate the efficacy of a combined microfinance and health leadership intervention we will conduct a trial among 1252 men in 60 camps that are randomly selected proportionally across four wards. Our primary hypothesis is that the combined microfinance and health leadership intervention will be associated with a lower incidence of sexually transmitted infections and other HIV risk behaviors and less perpetration of violence against female sexual partners over time among men in camps randomized to the intervention as compared to men in camps randomized to the control condition. We also hypothesize that men’s hope for, and orientation towards, the future, as well as the support, social influence and the collective efficacy of their networks, will mediate the effect of the intervention on these outcomes.

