# 9. STATISTICAL CONSIDERATIONS

## 9.1 Quantitative Statistical Analysis Plan

## 9.1.1 Sample Size, Power Calculations and Effect Size

The choice of 60 camps randomized into two groups is based upon evidence generated in our previous study and likely incidence estimates available from published studies with similar populations in Tanzania and other countries in Africa. We estimate average camp sizes of 36.2 sexually active males and 52 total males. STI measures of ulcer, discharge, any symptom, and any STI were used as possible sexual outcome measures, with condom use and sexual and/or physical violence perpetration our behavioral outcome measures. Based upon our previous study we computed intraclass correlation (ICC) estimates between 0.00 and 0.01 for sexually transmitted diseases and 0.00-0.032 for behavioral measures. Given average camp sizes and ICC estimates we have inflated sample size estimates assuming simple random sampling with design effects ranging from 1.4 to 2.3. All sample estimates assumed an attrition of 20%. Given a sample size of 1955 sexually active males and 2808 total males in 54 camps we will have 80% power (2-sided, α=0.05) to detect the protective effect of the intervention (OR) of 0.32 for ulcer, 0.59 for discharge, 0.61 for any STI symptom, 0.50 for syphilis, and 0.66 for any STI. We will be able to detect protective effects of 0.74, 0.68 and 0.65 in condom use for those sexually active, for all males, and for sexual or physical violence perpetration in all males, respectively. Statistical power to detect mediation is expected to be high based on the simulation results of Fritz and MacKinnon where a total sample size of 539 was sufficient for .80 power to detect the most conservative simulated mediation effect.([Fritz & MacKinnon, 2007](#_ENREF_27))

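### The 80% power in section 9.1.1 is for 2,808 men in 54 camps; the trial described has about 1,250 men in 60 camps and no stated power

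*Protocol*

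**What the plan says.** Section 9.1.1 opens by justifying 60 camps. Its cluster-size assumption is "We estimate average camp sizes of 36.2 sexually active males and 52 total males". It reports "intraclass correlation (ICC) estimates between 0.00 and 0.01 for sexually transmitted diseases and 0.00-0.032 for behavioral measures", inflates the sample "with design effects ranging from 1.4 to 2.3", and assumes 20% attrition throughout. It then gives the power statement: "Given a sample size of 1955 sexually active males and 2808 total males in 54 camps we will have 80% power", two-sided at 5%. The detectable odds ratios that follow include 0.66 for any STI and 0.65 for sexual or physical violence in all males.

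Elsewhere the trial has a different size. The Protocol Summary, under Study Size, gives "1249 male camp members". Section 3.2.3 says "we will conduct a trial among 1252 men in 60 camps". Section 5.4 puts 30 of the 60 camps in the control condition. Sections 3.3 and 6.6 have all men tested for STIs at the end of the study, not only the sexually active.

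**The concern.** The power statement and the trial description do not concern the same sample. The camps differ (54 against 60), the men differ (2,808 against 1,249 or 1,252), and above all the men per camp differ (52 against about 21). Smaller camps reduce the design effect and six more camps help, so it has to be checked whether these offset the loss of more than half the men.

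Violence and STI are the two primary endpoints. If the text stands, a null result would be read as coming from a trial with 80% power at odds ratios of 0.65 to 0.66, although the protocol contains no calculation supporting that for the men it will enrol.

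**Working it through.** **Inputs.** From section 9.1.1: 54 camps, 52 men per camp (36.2 sexually active), ICC 0-0.01 for STI and 0-0.032 for behaviour, 20% attrition, 80% power at two-sided 5%. From the Protocol Summary and section 3.2.3: 1,249 or 1,252 men, 60 camps.

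**What reproduces.** 54 × 52 = 2,808 and 54 × 36.2 = 1,954.8, the stated 1,955. With 20% attrition a camp has 52 × 0.8 = 41.6 men. The design effect 1 + (m − 1) × ICC is then 1 + 40.6 × 0.01 = 1.41 and 1 + 40.6 × 0.032 = 2.30, matching the stated 1.4 to 2.3. At the full 52 men it would be 1.51 and 2.63, so 2,808 is evidently the number before attrition.

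**What cannot be reproduced.** The 80% itself, because no control rate is given for any endpoint. It is attainable: for violence at a design effect of 2.3 it needs about 26.5% in controls. I therefore take it as true and rescale.

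**Size of the mismatch.** 2,808 / 1,249 = 2.2. Men per camp: 1,249 / 60 = 20.8 (1,252 / 60 = 20.9).

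**Rescaling.** Effective size is N / design effect. Power in the trial described = Φ(2.802 × √(effective size, trial / effective size, plan) − 1.960), where 2.802 = 1.960 + 0.842. The same ICC is used on both sides.

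Violence, odds ratio 0.65. The plan retains 2,808 × 0.8 = 2,246 men. The trial retains 1,249 × 0.8 = 999, or 16.7 per camp.

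| ICC | Effective, plan | Effective, trial | Power, 20% attrition | Power, 1,249 retained |
|---|---|---|---|---|
| 0 | 2,246 | 999 | 46% | 55% |
| 0.01 | 1,598 | 864 | 54% | 62% |
| 0.02 | 1,240 | 761 | 59% | 66% |
| 0.032 | 977 | 666 | 64% | 70% |

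Worked line at ICC 0.032: the trial's design effect is 1 + 15.65 × 0.032 = 1.50; 999 / 1.50 = 666; 666 / 977 = 0.681; Φ(2.802 × 0.825 − 1.960) = Φ(0.352) = 64%. A direct two-proportion calculation at a 26.5% control rate gives the same 64%.

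Any STI, odds ratio 0.66. The plan retains 1,955 × 0.8 = 1,564 sexually active men. Applying the planning ratio 36.2 / 52 = 0.696 to the 999 retained men gives 696 sexually active.

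| Men analysed | ICC | Effective, plan | Effective, trial | Power, 20% attrition | Power, 1,249 already net |
|---|---|---|---|---|---|
| Sexually active | 0 | 1,564 | 696 | 46% | 55% |
| Sexually active | 0.01 | 1,222 | 629 | 52% | 60% |
| All men | 0 | 1,564 | 999 | 61% | 71% |
| All men | 0.01 | 1,222 | 864 | 65% | 74% |

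Using 1,252 instead of 1,249 moves the violence figures by 0.1 point or less.

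**Do the six extra camps help?** At 52 men per camp they would: 60 × 52 = 3,120 men gives Φ(2.802 × √(60/54) − 1.960) = 84%. The loss comes entirely from having about 21 men per camp.

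**The case against.** The mismatch is plain on the page. The strongest objection is to drawing a firm power figure from it.

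- A reader might infer that power for violence is 64%. The documents do not support a single value. The ICC of 0.032 is only the top of a range for all behavioural measures, no control rate is stated, and nothing says whether 1,249 is before or after losses. With matched ICCs, 64% is also the most favourable point of the 46-64% range. This objection stands.
- A reader might infer that the trial is shown to lack 80% power for violence. Section 1.7 reports that 41% of men in the earlier camp survey had ever perpetrated violence. At that control rate, with 999 men, power at odds ratio 0.65 would be about 76% at ICC 0.032 and up to 90% at ICC 0. But 41% is a lifetime figure, section 7.3 collects both lifetime and 12-month items, and at 41% and ICC 0.032 the planned design would have had about 90%, not the stated 80%. So 41% does not appear to be the rate behind section 9.1.1. The case still shows that low power is not proven outright.
- A lower violence ICC might seem to rescue the trial. It does so only if 0.01 is used for the trial while the plan keeps a design effect of 2.3. With the same ICC on both sides, ICC 0.01 gives 54%, lower than at 0.032.
- Section 9.1.1 lists any STI beside ulcer, discharge, symptoms and syphilis, and never says that 0.66 refers to the NG/TV/CT endpoint. That link is an inference. If the plan used a design effect of 1.4 for any STI, power at ICC 0.01 in the trial is 56% (sexually active) or 69% (all men), and at most 77% without attrition.
- The gap between 1,249 and 1,252 is editorial. That is right.

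Section 9.1.1 may also be a design-stage justification kept after the sample changed. If so, the protocol does not say so and presents it as the power the trial will have.

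**Conclusion.** Wrong as written. The stated 80% power and all the detectable odds ratios apply to a sample about 2.2 times the one the protocol describes, and no stated power applies to the trial itself. That much follows from the text without any assumption.

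The size of the loss is conditional. It takes the stated 80% as true and uses the same ICC for plan and trial over the stated ranges. Power at the quoted odds ratios is then about 46-64% for violence and 46-65% for any STI with 20% attrition (for STI, 46-52% if only sexually active men count and 61-65% if all men do). If 1,249 is already net of attrition, it is about 55-70% and 55-74%. On none of these matched readings do the extra camps and smaller design effect restore 80%. The documents do not support a single figure, nor a flat statement that either endpoint is underpowered, because the control rates and endpoint-specific ICCs are missing.

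**What to change.** In section 9.1.1, reconcile 54 with 60 camps, and 2,808 men with the enrolment figure. Settle that figure as either 1,249 or 1,252 throughout, and say whether it is before or after attrition. Then restate the power or the detectable odds ratio for each primary endpoint (violence; NG/TV/CT) at about 1,250 men in 60 camps with 20% attrition. Show for each the control rate and its time window, the ICC, and whether all men or only the sexually active are analysed. The sponsor should supply these inputs; odds ratios back-calculated from unknown control rates should not be written in. If the 54-camp calculation is kept as a record of the planning stage, label it so.

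The cost is protocol wording and one recalculation. No extra participants are needed, but the stated power will be less favourable.

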## 3.3 Study Duration and Endpoints

The intervention will be implemented for two years, and the total duration of the trial will be 5 years. **The primary endpoints** are sexually transmitted infections including Neisseria gonorrhea (NG), Trichomonas vaginalis (TV), Chlamydia trachomatis (CT), and perpetration of physical or sexual violence against a sexual partner. A random sample of 50% of participating men will be flagged for an STI test at baseline to assess relative prevalence, and all men will be tested at endline. A test of relative prevalence at baseline will aid in establishing equivalency in the two arms; any lack of equivalency then will be controlled for appropriately at endline. All participants will complete a behavioral assessment at baseline, 12 months and 30 months to assess secondary objectives. **Secondary endpoints** are HIV risk and protective behaviors including: gender equity, alcohol and drug use, sexual relations and risk behavior, uptake of HIV counseling and testing; unprotected sexual intercourse; consistent condom use; delay of sexual debut; number of sexual partners, and sexual concurrency. **Key mediators** are hope, future orientation, social cohesion, collective efficacy, emotional distress, sexual networks, social support and social influence.

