## 7.2 Primary Endpoint - STI Prevalence

For the proposed study, men will provide a first-catch urine specimen for NG, CT and TV testing by polymerase chain reaction (PCR). The introduction of nucleic acid amplification tests (NAATs), including PCR for the detection of sexually transmitted pathogens, has provided critical new tools for diagnosis of infections with Neisseria gonorrhea (NG), Chlamydia trachomatis (CT) and Trichomonas vaginalis (TV). NAATs are substantially more sensitive than culture or antigen detection assays, and specific detection of multiple STI pathogens in men is possible using traditional urethral specimens and, importantly, in noninvasive urine specimens. Study participants who are identified with NG, CT, or TV will be offered treatment according to the standard of care in Tanzania: NG (Ceftriaxone), CT (Doxycycline), TV (Metronidazole).

Blood will be obtained for serologic tests to detect antibodies indicating infection with HIV. We will use Immnochromatographic tests (ICT), which are Alare Determine ^TM^ HIV 1/2 as Test 1 and Unigold ^TM^ HIV as Test 2. An Immuno-Chromatographic test (ICT) is used for the qualitative detection of antibodies to the human immunodeficiency virus (HIV) type 1 and 2 in blood. The blood sample flows along the strip and if HIV antibodies are present, the antigen/antibody complex binds with a conjugate forming red band. If antibodies to HIV are absent no red band is formed. To ensure assay validity, a procedural control band is incorporated into assay device.

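### The STI odds ratios in section 9.1.1 are for outcomes the trial does not use, plus an undefined *any STI*, so the stated 80% power cannot be tied to the NG/CT/TV PCR endpoint

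*Protocol*

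**What the plan says.** Section 3.3 says the primary endpoints "are sexually transmitted infections including Neisseria gonorrhea (NG), Trichomonas vaginalis (TV), Chlamydia trachomatis (CT"), together with violence perpetration. Section 7.2 fixes the measurement: "men will provide a first-catch urine specimen for NG, CT and TV testing by polymerase chain reaction (PCR"). In the same section, blood is used for HIV antibodies. Section 6.6 gives the month-30 panel as NG, TV, CT and HIV.

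Section 9.1.1 sizes the STI side of the trial differently. It says that "STI measures of ulcer, discharge, any symptom, and any STI were used as possible sexual outcome measures". It then starts from this base: "Given a sample size of 1955 sexually active males and 2808 total males in 54 camps". At "80% power (2-sided, α=0.05") it reports detectable odds ratios of "0.32 for ulcer, 0.59 for discharge, 0.61 for any STI symptom, 0.50 for syphilis, and 0.66 for any STI". Syphilis has an odds ratio but is missing from the section's own list of STI measures. The section names neither NG, CT or TV nor PCR, does not define *any STI*, and gives no control-arm rate for any STI outcome. It says only that likely incidence came from the previous study and published work.

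**The concern.** A power statement belongs to an outcome. Four of the five STI odds ratios belong to outcomes that section 7 does not list, and one of those four, syphilis, has no test anywhere in the protocol. The fifth could be the primary endpoint, but the text does not say so and omits the rate needed to check it.

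This is more than a detail that could be left to a statistical analysis plan. The protocol itself states the power basis and states it for outcomes it does not analyse. A reader would naturally credit the NG/CT/TV endpoint with 80% power at an odds ratio of 0.66, and the document does not establish that. For a binary outcome, the odds ratio detectable with a fixed number of men depends heavily on control prevalence. Without it, the protocol's figures do not show whether the trial can answer its STI question.

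**Working it through.** **Which outcomes the trial has**

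| Outcome powered in 9.1.1 | Odds ratio | Place in the trial |
|---|---|---|
| Ulcer | 0.32 | Not listed in section 7 |
| Discharge | 0.59 | Not listed in section 7 |
| Any STI symptom | 0.61 | Not listed in section 7; section 10.2 offers a nurse symptom check, as a service, to men not selected for specimens |
| Syphilis | 0.50 | No test described; blood is for HIV (7.2, 6.6) |
| Any STI | 0.66 | Not defined; may or may not be NG/CT/TV |

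**Inputs from 9.1.1**

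- Camp size: "We estimate average camp sizes of 36.2 sexually active males and 52 total males".
- Intraclass correlations (ICCs): "estimates between 0.00 and 0.01 for sexually transmitted diseases and 0.00-0.032 for behavioral measures".
- Design effects 1.4 to 2.3, attrition 20%, two-sided α 0.05, power 80%.

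**What reproduces**

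- Men: 54 × 36.2 = 1,954.8, stated as 1,955; 54 × 52 = 2,808.
- Design effect, 1 + (m − 1) × ICC with m after attrition: for all males, m = 52 × 0.8 = 41.6, giving 1 + 40.6 × 0.01 = 1.41 and 1 + 40.6 × 0.032 = 2.30. These are the stated 1.4 and 2.3.
- For sexually active men, m = 36.2 × 0.8 = 28.96, giving 1 + 27.96 × 0.01 = 1.28. At ICC 0 it is 1.0.

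The odds ratio of 0.66 cannot be reproduced, because its control prevalence is missing.

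**Solving back for the prevalence that 0.66 requires**

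Effective men per arm are n = 1,955 × 0.8 / 2 / design effect: 782 at 1.0, 611 at 1.28 and 559 at 1.4. With control prevalence p and odds ratio θ, intervention prevalence is q = θp / (1 − p + θp). Power is Φ{[|p − q| − 1.96·SE₀] / SE₁}, where SE₀ = √(2p̄(1 − p̄)/n), p̄ = (p + q)/2 and SE₁ = √([p(1 − p) + q(1 − q)]/n). Setting power to 80% at θ = 0.66 gives p = 16.1% (design effect 1.0), 21.6% (1.28) and 24.2% (1.4).

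The one STI rate in the protocol is in section 1.7: 21% of men in the previous study had at least one symptom in the past 4 weeks. Used as the control rate, it gives a detectable odds ratio of 0.69, 0.66 and 0.64 at the three design effects. The stated symptom figure is 0.61, so that rate does not reproduce it either.

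**Illustration under assumed NG/CT/TV prevalence (1,955 men, 20% attrition)**

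| Control prevalence (assumed) | Prevalence at OR 0.66 | Power, DE 1.0 | Power, DE 1.28 | Power, DE 1.4 | Detectable OR, ICC 0 / 0.01 (DE 1.0 / 1.28) |
|---|---|---|---|---|---|
| 5% | 3.4% | 37% | 30% | 28% | 0.45 / 0.40 |
| 10% | 6.8% | 62% | 51% | 48% | 0.59 / 0.54 |
| 15% | 10.4% | 77% | 67% | 63% | 0.65 / 0.61 |
| 20% | 14.2% | 87% | 77% | 74% | 0.69 / 0.65 |
| 25% | 18.0% | 92% | 84% | 81% | 0.71 / 0.68 |
| 30% | 22.0% | 95% | 89% | 86% | 0.73 / 0.69 |

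**The case against.** *Any STI* may well be the NG/CT/TV composite. Section 3.3 words the endpoint as sexually transmitted infections including those three, which is close to the label in 9.1.1. If control prevalence is about 25%, the planned 1,955 men give 81–92% power at 0.66, so the stated figure would stand. Nor is there an arithmetic slip: the numbers of men and the design effects reproduce.

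This stands, and it rules out three stronger readings.

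- **That 0.66 belongs to a different, more common outcome.** At a common design effect of 1.4, the stated odds ratios imply 24% for *any STI* against 16.5% for any symptom, which invites that inference. But STI intraclass correlations of 0.00 to 0.01 allow the design effect to differ by outcome. *Any STI* at 1.0 implies 16.1%, and any symptom at 1.4 implies 16.5%, so the ordering disappears. A higher rate for *any STI* would also be compatible with sensitive PCR testing.
- **That the STI endpoint has no power statement at all.** An undefined term cannot be shown to exclude NG/CT/TV.
- **That the trial is underpowered for STI.** The low-prevalence rows are assumptions; the protocol gives no NG/CT/TV rate.

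Two limits on the evidence also hold. The survey in Appendix D contains no ulcer, discharge or symptom item, but it lacks several measures that section 7 describes, so it is not complete proof. The firmer ground is that section 7 lists no such outcome. The study size of 1,249 or 1,252 men in 60 camps (Protocol Summary, section 3.2.3) against 1,955 sexually active men in 54 camps is a separate discrepancy, over different denominators, and is not counted in the size of this point.

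None of this supplies the missing definition or control rate, or makes the other four outcomes endpoints.

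**Conclusion.** The point holds as a mismatch of definition. Four of the five STI odds ratios in 9.1.1 are for outcomes the trial does not use, and the fifth can be neither linked to the PCR endpoint nor checked. The stated 80% power at 0.66 is right for NG/CT/TV only if *any STI* means that composite and control prevalence is roughly 16–24%, depending on the design effect. Below that range power falls, to 48–62% at 10% and 28–37% at 5%; above it the claim is met.

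These figures rest on the protocol's 1,955 men, 20% attrition, equal arms, design effects of 1.0 to 1.4 and a normal approximation for two proportions. The prevalences are assumed. The gap concerns the STI endpoint only; violence perpetration has its own stated odds ratio of 0.65.

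**What to change.** In section 9.1.1:

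1. Delete the odds ratios for ulcer, discharge, any STI symptom and syphilis.
2. Define the sized outcome as PCR-positive for at least one of NG, CT or TV at month 30.
3. State whether the denominator is all men tested or sexually active men. Section 9.1.1 uses sexually active men, while section 6.6 tests all eligible and consenting men.
4. Replace the single 0.66 with a small table of detectable odds ratios at the trial's actual number of men and camps, over a control prevalence range that spans break-even (for example 5–30%) and ICC 0 to 0.01.

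Prevalence in the half tested at baseline may inform the range. Men found positive then are to be offered treatment (sections 7.2 and 10.9), so baseline prevalence may not predict prevalence at month 30.

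The cost is a few sentences and one table, with no change to conduct. The detectable odds ratio may turn out better or worse than 0.66, depending on prevalence and the number of men.

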### 9.1.4 Mediation Sampling and Analytical Technique

In the event that program effects are identified, we will estimate path coefficients in multiple mediator models and generate bootstrapped confidence intervals for total and specific indirect effects of one or more mediator models using the Mplus program Version 6.11.([Pituch, Stapleton, & Kang, 2006](#_ENREF_65)) We will assess simple and multiple mediation in the relationships between the microfinance intervention condition, intervention mediators including hope, future orientation, social cohesion, social support, emotional distress, gender equity, conflict, alcohol and drug use, HIV stigma, perceived social support, collective efficacy, sexual relationships and risk behavior, attitudes towards HIV risk and intimate partner violence, work and expenditures, sexual relationships and risk behavior, and social and sexual network norms.

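### The 539-person benchmark in Section 9.1.1 does not support high mediation power for STI: for the same effect, power runs from about 40% to 84% over an STI prevalence of 5-21% that the protocol does not state

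*Protocol*

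**What the plan says.** The last sentence of Protocol Section 9.1.1 reads: "Statistical power to detect mediation is expected to be high based on the simulation results". The only support is a published simulation in which "a total sample size of 539 was sufficient for .80 power to detect the most conservative simulated mediation effect". The sentence gives no path sizes, mediator ICC, outcome frequency or attrition.

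The main-effect figures in the same paragraph are treated differently. They use "intraclass correlation (ICC) estimates between 0.00 and 0.01 for sexually transmitted diseases and 0.00-0.032 for behavioral measures", and the authors write that "we have inflated sample size estimates assuming simple random sampling with design effects ranging from 1.4 to 2.3", with 20% attrition. Those figures rest on 1,955 sexually active men and 2,808 men in total, in 54 camps. The Protocol Summary gives a study size of 1,249 men, and Section 3.2.3 gives 1,252 men in 60 camps.

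The Protocol Summary names the mediated outcomes: "In the event that program effects are identified, the degree to which the following mediate the multi-level intervention on STI and gender-based violence". Section 9.1.4 plans to "generate bootstrapped confidence intervals for total and specific indirect effects of one or more mediator models", and cites a study of bootstrap methods for mediation in cluster randomized trials for the method.

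**The concern.** The benchmark does not match the analysis that it is meant to support. Treatment is assigned to camps, so the path from intervention to mediator is a between-camp contrast. The outcomes are yes/no, so the path from mediator to outcome carries less information per man, and much less if infection is uncommon. A single count that depends on neither the ICC nor the outcome frequency cannot describe power for both STI and violence.

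Mediation is a secondary objective (Section 2.3) and part of the hypothesis (Section 3.2.3). If the protocol calls the test highly powered, a non-significant indirect effect on STI through hope, collective efficacy or another mediator invites the conclusion that the pathway does not operate. The test may in fact be unable to tell.

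**Working it through.** **Inputs from the Protocol.** Benchmark 539 for 80% power (9.1.1). Two-sided α of 0.05, stated for the main effects and assumed here for mediation. ICC up to 0.032 for behavioural measures, assumed for the mediators because none is given for them. Attrition 20%. 60 camps and 1,249 men (Protocol Summary). Sexually active share 36.2/52 = 0.696 (9.1.1). Violence ever perpetrated 41% (1.7). No NG/CT/TV prevalence is stated.

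**Step 1: what 539 implies.** It cannot be reproduced from protocol inputs, because no path size is given. Assume independent observations, a continuous mediator and outcome, equal standardised paths a = b, and a joint test of both paths. Then power = [Φ(a√539 − 1.96)]² = 0.80 requires 0.894 per path, so a√539 = 3.21 and a = 0.138.

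**Step 2: clustering and attrition only.** Retained men: 1,249 × 0.8 = 999, or 16.65 per camp. Design effect: 1 + 15.65 × 0.032 = 1.50. Effective N: 999/1.50 = 666. First path: noncentrality 0.138 × √666 = 3.57, and power on 58 df is 0.94. Second path, continuous outcome: 0.138 × √999 = 4.37, power 0.99. Joint power is about 0.93, or 0.89 if both paths are deflated. Effective N remains above 539.

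**Step 3: binary outcome.** The first path stays at 0.94. The second path is computed in two ways:
- Logistic: z = 0.138 × (π/√3) × √[999 p(1−p)].
- Latent threshold: z = 0.138 × √(999 × e), with e = φ(t)²/[p(1−p)] and t the normal quantile of p.

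| Outcome frequency p | Logistic z | Joint power | e | Threshold z | Joint power |
|---|---|---|---|---|---|
| 5% | 1.73 | 0.38 | 0.224 | 2.07 | 0.51 |
| 10% | 2.38 | 0.62 | 0.342 | 2.56 | 0.68 |
| 15% | 2.83 | 0.76 | 0.426 | 2.85 | 0.76 |
| 21% | 3.23 | 0.84 | 0.501 | 3.09 | 0.82 |
| 41% (violence) | 3.90 | 0.91 | 0.625 | 3.46 | 0.88 |

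Simulations with 60 camps and cluster-robust tests gave 63-66% at 10%, in line with the table.

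**Step 4: sexually active men only.** 999 × 0.696 = 695 men, 11.6 per camp, design effect 1.34, first-path power 0.87. Joint power is about 57-58% at 15% and 64-67% at 21%.

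**Step 5: what prevalence does the plan imply?** Section 9.1.1 gives a detectable OR of 0.66 for any STI. Solving the two-proportion formula at 80% power gives an average prevalence of about 15% (1,955 men, design effect 1.35) to 21% (1,955 × 0.8 = 1,564 men, design effect 1.4). The lower design effect fits sexually active men: 1 + 35.2 × 0.01 = 1.35. If infection is negligible in the other men, prevalence among all men is 0.696 × 15-21% = about 10-15%, where the table gives 62-76%.

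**Step 6: the sample in the power paragraph.** 1,564 retained sexually active men in 54 camps is 29 per camp, with a design effect of 1.90 and an effective N of 825. Joint power for STI at 10% is then 82-87%, against 62-68% with 999 men.

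**The case against.** Several objections have force:

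- The source of the 539 is not at hand. Independent observations, a continuous outcome and paths of 0.138 are assumptions, and every power figure above inherits them. A Sobel-type test would imply different paths: at 0.14 it needs 801 people, not 539. The check uses joint significance, whereas Section 9.1.4 plans bootstrapped intervals.
- If 0.138 is read as a standardised coefficient on the observed yes/no outcome, joint power is about 93% and no shortfall appears.
- Mediation is analysed only if program effects are found, 539 did not size the trial, and intervals for the indirect effects are already planned. No section says that a null result will be read as absence of a pathway.
- For violence the protocol's description survives: 88-91% at 41%. That figure is for violence ever perpetrated. A 12-month rate would be lower, and so would the power.

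A reader might go further and infer that STI mediation power in this trial is 50-70% and that 80% is out of reach. The documents do not support that. It requires a particular prevalence, analysis population and effect scale, none of them stated; at 21% among all retained men the result is 82-84%. A reader might also blame clustering and attrition, but alone they leave about 93%. Nor should the design effect of 2.3 be applied here: 1 + (52 × 0.8 − 1) × 0.032 = 2.3, so it belongs to camps of 52 members, not to about 17 retained men per camp.

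What stands is that the benchmark takes account of none of this, so it cannot carry the claim for STI.

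**Conclusion.** The point holds in a limited form. One unadapted count of 539 does not justify high mediation power for both outcomes. For violence, power is probably adequate. For STI it depends on figures that the protocol omits, and it is below 80% over much of the plausible range: about 40-50% at 5% prevalence, 62-68% at 10%, 76% at 15%, and above 80% only towards 21%. The prevalence implied by the plan's own OR of 0.66 puts it at about 62-76% for all retained men, or 57-67% if only sexually active men are analysed.

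These results assume paths of 0.138 on a latent scale, a mediator ICC of 0.032 and 20% attrition. They ignore the additional clustering created in Section 4.1.4, where camps from the same geographic group share a condition; that would lower power somewhat. The shortfall comes from the binary, possibly infrequent STI outcome and from a sample smaller than the one in the power paragraph.

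**What to change.** Replace the last sentence of Section 9.1.1 with mediation power, or the smallest detectable indirect effect, computed separately for STI and violence. Use 60 camps and about 1,000 retained men, and state the path sizes and their scale, the mediator ICC, the analysis population and a range of STI prevalence. Remove the statement that power is expected to be high for STI. Give a range tied to its assumptions rather than one substitute figure, and use a design effect that matches the actual number of men per camp. Add that a non-significant indirect effect on STI will be reported with its confidence interval as inconclusive, not as absence of mediation.

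The cost is a short simulation and a few sentences, with no extra participants or data. The downside is that the stated mediation power for STI becomes less favourable.
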